**Fig. 2 fig2:**
[figure not shown]
*The RISE-Up EA+ Conceptual Model.* The conceptual model outlines study analysis plans to 1) examine if sex moderates the association between mobility opportunity, brain health and general cognitive ability; 2) investigate links between mobility opportunity and health mechanisms (inflammation and microbiome), and whether those links are moderated by sex; 2a) conduct an exploratory analysis to test whether sex and *ApoE*-ε4 interact to predict health profiles (proinflammatory blood and stool profiles); 3) assess if brain health and health mechanisms (inflammation and microbiome) mediate the link between mobility opportunity and general cognitive ability and whether this is moderated by sex. Created in https://BioRender.com.

In addition to our primary Aim 2, we also have an exploratory Aim 2 to test whether sex and *ApoE*-ε4 status interact to predict inflammatory markers and microbiome enrichment for inflammatory genes and pathways, especially in females. For the exploratory analysis, we hypothesize (H3) that *ApoE*-ε4 carrying mobility opportunity females will have the most proinflammatory blood and stool profiles.3.**Determine whether the association between mobility opportunity and GCA is mediated by brain health, inflammatory blood markers, and the microbiome (parallel mediators) and moderated by sex.** We hypothesize (H4) that females exposed to mobility opportunity during adolescence, relative to males exposed to mobility opportunity, will have more pro-inflammatory profiles in blood and stool (increased physical health risks), and worse brain health (diminished activation in prefrontal areas supporting cognitive function) during early adulthood, which will in turn mediate the association with GCA in early adulthood. We expect to see these sex differences indicating sex-specific-pathways within the mobility opportunity group, reflecting greater impact of wear and tear over time from mobility opportunity in females compared to males. In turn, we propose that these may be early markers for increased AD risk later in life that may be realized over time. However, within females at this age, we still expect to see that mobility opportunity females will have better GCA relative to static opportunity females.

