## Study aims & hypotheses

2

In the RISE-Up EA+ Study, we will collect measures of striving-associated stress through self-report. We will quantify health risks by indexing brain-gut axis function via inflammatory markers in blood, the microbiome metagenome in stool, *ApoE* gene allele via buccal swab, brain health through Magnetic Resonance Imaging (MRI), and general cognitive ability through standardized neurocognitive tests. Using these measures, we will examine how sex moderates the links between youths afforded mobility opportunity by randomization into high performance schools vs. those who were not (i.e., waitlisted) and brain health, general cognitive ability, inflammatory markers, and the microbiome (see Fig. 2 for the conceptual model). Both sex assigned at birth and gender identity might contribute to potential differences observed in this study and we will aim to try to parse these constructs when we can, highlighting that sex-related differences may be, in part, due to stress related to gender roles and expectations. The aims of our study are as follows:1.**Identify the impact of mobility opportunity on young adult general cognitive ability (GCA) and brain health (which we propose will link with later life resilience to AD), and determine if those associations are moderated by sex.** We hypothesize (H1) that mobility opportunity will be associated with worse brain health in females, but better brain health in males, relative to static opportunity. Second, we hypothesize (H1.2) that mobility opportunity will be associated with greater GCA in both males and females, relative to static opportunity.2.**Establish links between mobility opportunity, inflammatory markers, and microbiome enrichment for inflammatory genes and pathways, and determine whether those links are moderated by sex and sex-related vulnerabilities (adolescent stress).** We expect (H2) that relative to static opportunity, mobility opportunity in females (but not males) will have a greater average expression of inflammatory genes in blood, and genes and pathways involved in inflammation in stool.

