### Recruitment & eligibility

3.1

The demographics of the original RISE-Up Study have been described extensively elsewhere (Wong et al., 2022; Dudovitz et al., 2018), but broadly consisted of 1270 participants (52.6% female, 47.4% male, median age 14.2) who were entering 9th grade in Fall 2013 or Fall 2014. Participants for the original study were largely recruited from and are representative of low-income neighborhoods in Los Angeles, with 1137 (89.5%) identifying as Latino (Dudovitz et al., 2018), and all applied for high-achieving charter high school admission lottery, with 694 students (54.6%) being admitted on the basis of random lottery (intervention/mobile group) and 576 students (45.4%) on the waiting list (control/static group). Recruitment for the RISE-Up-EA+ extension study is dependent upon previous participation in the RISE-Up-EA follow up study, which is ongoing (see Fig. 1 for a timeline of study phases). A subsample of 300 participants aged 24-26 years old who previously consented to follow-up contact will be included in the extension study. Detailed contact information has been maintained for prior participants, enabling digital communication via text message and email. Interested respondents will schedule a phone screening, during which a study coordinator will administer a brief screening interview and obtain informed consent. During this phone screen, the research staff will also explain procedures for the extension study. Participants who meet eligibility criteria for the study (including MRI safety screening) and agree to participate will be scheduled for a three and a half hour on-site in-person session at the University of California, Los Angeles (UCLA) where they will complete a magnetic resonance imaging (MRI) scan, behavioral tasks, cognitive assessments, and will be administered biospecimen samples (see Fig. 3 for session flow). Prior to their in-person session, participants will be consented and will be administered questionnaires to complete remotely or they will have the opportunity to complete questionnaires at the in-person session. The protocol for this study has been approved by the Medical Institutional Review Board of the University of California, Los Angeles (IRB#24-000281).

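### H4 reads a female-male gap inside the mobility arm as an effect of mobility, which does not match the two-arm, sex-moderated analysis that Aim 3 implies

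*Protocol article*

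**What the plan says.** The relevant text is in Section 2 (Study aims & hypotheses) of the protocol article; H4 is printed after the Fig. 2 legend.

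- **H4, comparison.** It predicts that "females exposed to mobility opportunity during adolescence, relative to males exposed to mobility opportunity, will have more pro-inflammatory profiles in blood and stool", and adds worse brain health, with these mediators then mediating the association with GCA.
- **H4, interpretation.** "We expect to see these sex differences indicating sex-specific-pathways within the mobility opportunity group, reflecting greater impact of wear and tear over time". The sentence ends by naming mobility as the source of this wear and by saying that females bear more of it than males.
- **H4, static comparator.** There is one, and it concerns cognition in females only: "mobility opportunity females will have better GCA relative to static opportunity females". None is given for inflammation, microbiome or brain health.
- **Aim 3 in the Fig. 2 legend.** The analysis is to "assess if brain health and health mechanisms (inflammation and microbiome) mediate the link between mobility opportunity and general cognitive ability and whether this is moderated"; the moderator named is sex. The Aim 3 heading says the same in substance.
- **H1.** "mobility opportunity will be associated with worse brain health in females, but better brain health in males, relative to static opportunity".
- **H2.** "relative to static opportunity, mobility opportunity in females (but not males) will have a greater average expression of inflammatory genes in blood".
- **What was random (Section 3.1).** Students were allocated by lottery: "being admitted on the basis of random lottery (intervention/mobile group) and 576 students (45.4%) on the waiting list (control/static group").

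**The concern.** The lottery allocated school opportunity. It did not allocate sex, and it says nothing about why females and males in the same arm differ. A female-male gap among lottery winners is the background sex difference plus any extra effect of mobility in females, and data from that arm alone cannot separate the two.

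The article itself gives reasons to expect background differences. Section 1.4 says obesity is more common in women, and Section 1.5 links obesity to pro-inflammatory gene expression. Section 1.5 also describes sex differences in microglial behaviour in rodents and a possible hormonal influence on gut microbiota. None of these depends on winning a school lottery.

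H4's mediation clause does not remove the difficulty. Inside one arm, mediation reduces to a path from sex to mediator to GCA, and ordinary sex differences can produce that path too.

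What is at stake is the causal-pathway claim of Aim 3. Judged as worded, the mediator part of H4 could be declared supported with no mobility effect. It could also be missed when a real differential effect is offset by a background difference in the opposite direction.

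**Working it through.** **1. The plan's own figures (Section 4).** Inputs: 150 mobile and 150 static, 1:1 female to male, alpha .025 two-sided, d = 0.36.

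- Two-sample t-test, df = 298: critical t = 2.253. Noncentrality = 0.36 / √(1/150 + 1/150) = 0.36 / 0.1155 = 3.12; power 80.6%.
- The exact 80% point is d = 0.3575, with noncentrality 3.10. The stated 0.36, 2.25 and 3.10 reproduce.
- Moderated-mediation figure (critical F 2.24, noncentrality 13.07), taking 5 numerator df (inferred; the article does not state it) and alpha .05:

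| N | Critical F | f² = 13.07/N |
|---|---|---|
| 300 | 2.245 (power 80.0%) | 0.044 |
| 150 | 2.277 | 0.087 |

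The stated f² of .04 and critical F of 2.24 fit N = 300. The power calculation therefore assumed both arms.

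**2. What each contrast estimates.** For one marker, let b be the background female-minus-male difference, and m_F and m_M the effects of mobility in females and males.

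- Static-arm gap = b
- Mobility-arm gap = b + (m_F − m_M)
- Mobility-arm gap minus static-arm gap = m_F − m_M

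H4 reads the second line as if it were the third. The two agree only if b = 0. The third line is also (mobile − static in females) − (mobile − static in males), which is the sex-by-mobility interaction.

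**3. Size of the problem with no mobility effect.** Set m_F = m_M = 0, so the mobility-arm gap is b. A 1:1 sex ratio gives 150/2 = 75 per cell. The standard error in SD units is √(1/75 + 1/75) = 0.1633, df = 148, and critical t is 2.264 at alpha .025 and 1.976 at .05. The article gives no background sex difference for these markers, so the values of b are assumptions. Section 4 sets .025 for the brain-health markers; both levels are shown.

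| Assumed b (SD) | Noncentrality b/0.1633 | Significant in H4's direction, alpha .025 | Same, alpha .05 |
|---|---|---|---|
| 0.2 | 1.22 | 15% | 23% |
| 0.3 | 1.84 | 34% | 45% |
| 0.5 | 3.06 | 79% | 86% |

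In 20,000 simulated studies per setting with the same b in both arms, the interaction test (75 per cell, df 296, alpha .025) rejected 2.5%, 2.5%, 2.6% and 2.5% of the time at b = 0, 0.2, 0.36 and 0.5. That is its nominal level.

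**4. Precision of the interaction.** Its standard error is √(4/75) = 0.2309. It has 80% power at a difference in differences of about 0.72 SD at alpha .025 (0.65 SD at .05). At 0.36 SD its power is about 25% at alpha .025.

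**The case against.** The strongest reply is that H4 states an expectation and does not specify a test. Nothing in the article prescribes a 75 v 75 comparison of females and males in the mobility arm. The Aim 3 heading and the Fig. 2 legend describe mediation of the mobility-GCA link moderated by sex, which requires both arms. The power figure fits 300 participants. H1 and H2 already predict sex-dependent effects on brain health and inflammation relative to static opportunity. Exact contrast coding is commonly left to an analysis plan, which is not shown here.

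Most of this stands. A reader might infer from H4 that the study discards the lottery or that its model leaves out the sex-by-mobility term. The documents do not support that: the places just listed point to a two-arm moderated model, and in such a model a constant sex difference is not credited to mobility.

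A reader might also take the percentages above as the chance that H4 as a whole would be supported. They are not. They are single-marker rates under assumed sex differences, whereas H4 asks for more inflammatory blood and stool profiles, worse brain health and mediation together. The joint probability cannot exceed that of the least likely component.

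The reply does not remove what H4 says. It names mobility males as the comparator and attributes the gap to mobility. That is an incorrect rule of inference in the text, and a later analysis plan that says something different would leave two versions of the hypothesis.

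**Conclusion.** The point holds as a mismatch between H4 and the analysis that Aim 3 implies. For the mediators, H4's contrast does not identify a mobility effect, and its mediator part can be met by a sex difference equal in both arms. With 75 per sex in the mobility arm and no mobility effect, that would happen per marker about 15% to 79% of the time at alpha .025 for assumed sex differences of 0.2 to 0.5 SD (23% to 86% at .05), against 2.5% for the interaction test at alpha .025. These rates depend on the assumed differences, equal cells and a single marker. No stated number in the power section is wrong on this account.

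**What to change.** Restate H4 as a difference in differences: the mobile-minus-static effect on each mediator, and the indirect effect of mobility on GCA, differs between females and males in the predicted direction. Test it with the sex-by-mobility term on the mediator path and the index of moderated mediation, using all 300 participants. Report the female-male gap within the mobility arm descriptively only, beside the same gap in the static arm.

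No new data are needed; one hypothesis and its contrast are reworded. The loss of precision shown in step 4 should be stated with the revised hypothesis, because the published d = 0.36 describes a 150 v 150 comparison and does not carry over to this interaction.

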## Methods

3

### Recruitment & eligibility

3.1

The demographics of the original RISE-Up Study have been described extensively elsewhere (Wong et al., 2022; Dudovitz et al., 2018), but broadly consisted of 1270 participants (52.6% female, 47.4% male, median age 14.2) who were entering 9th grade in Fall 2013 or Fall 2014. Participants for the original study were largely recruited from and are representative of low-income neighborhoods in Los Angeles, with 1137 (89.5%) identifying as Latino (Dudovitz et al., 2018), and all applied for high-achieving charter high school admission lottery, with 694 students (54.6%) being admitted on the basis of random lottery (intervention/mobile group) and 576 students (45.4%) on the waiting list (control/static group). Recruitment for the RISE-Up-EA+ extension study is dependent upon previous participation in the RISE-Up-EA follow up study, which is ongoing (see Fig. 1 for a timeline of study phases). A subsample of 300 participants aged 24-26 years old who previously consented to follow-up contact will be included in the extension study. Detailed contact information has been maintained for prior participants, enabling digital communication via text message and email. Interested respondents will schedule a phone screening, during which a study coordinator will administer a brief screening interview and obtain informed consent. During this phone screen, the research staff will also explain procedures for the extension study. Participants who meet eligibility criteria for the study (including MRI safety screening) and agree to participate will be scheduled for a three and a half hour on-site in-person session at the University of California, Los Angeles (UCLA) where they will complete a magnetic resonance imaging (MRI) scan, behavioral tasks, cognitive assessments, and will be administered biospecimen samples (see Fig. 3 for session flow). Prior to their in-person session, participants will be consented and will be administered questionnaires to complete remotely or they will have the opportunity to complete questionnaires at the in-person session. The protocol for this study has been approved by the Medical Institutional Review Board of the University of California, Los Angeles (IRB#24-000281).

**Fig. 3 fig3:**
[figure not shown]
*The RISE-Up EA+ In-Person Session Flow.* Eligible participants will be scheduled for in-person sessions at UCLA. During the pre-scan section of the session, participants will review consent forms, complete updated MRI safety screening forms, and will be trained on fMRI tasks that they will complete inside the scanner. During the MRI scan, we will collect multimodal imaging data including structural, functional, and neurometabolic data. After the scan, participants will contribute biological samples, complete the NIH-Toolbox, and provide self-report questionnaires if these were not completed prior to the in-person session. Created in https://BioRender.com.

*Exclusion Criteria:* Exclusionary criteria include typical MRI contraindications (e.g., the presence of braces or metal implants). Due to the requirements of an in-person study visit, previously-enrolled participants who have relocated out of state will be excluded. Since the original RISE-Up study's inception, only 30 participants (2.4%) have moved entirely out of California.

### Measures

3.2

#### Self-report questionnaires

3.2.1

A range of assessments have been collected and examined in the original RISE-Up cohort since baseline across multiple longitudinal timepoints in the following domains that will be used to supplement the extension study, including assessments examining socioemotional factors, important life events and SES factors, health behaviors and conditions, arrest and incarceration data, and risk taking. In addition to these measurements, the RISE-Up-EA+ extension study will also administer a range of self-report surveys to participants assessing stressful exposures, mental health, and physical health below.

##### Stressful exposures

3.2.1.1

Early life adversity will be assessed using the Childhood Trauma Questionnaire (CTQ) which assesses physical, emotional and sexual abuse and physical and emotional neglect in 70 items scored on a 5-point Likert scale (α = .95) (Bernstein et al., 1994, 2003). Current stress will be assessed using the 10-item Perceived Stress Scale (PSS), which asks participants to rate how unpredictable, uncontrollable, and overloaded they found their lives over the last month on a 5-point Likert scale (α > .84) (Cohen et al., 1983). Additionally, we will assess discrimination experiences using the 9-item Everyday Discrimination Scale, which asks participants to rate the frequency of discriminatory actions experienced, and what characteristic they attribute those actions to (α = .63 for lifetime and .80 for everyday). (Krieger et al., 2005; Williams et al., 2003; Taylor et al., 2004).

##### Emotional and mental health

3.2.1.2

Mental health will be assessed using a short form of the Mood and Anxiety Symptom Questionnaire (Mini-MASQ - 26 items), which asks respondents to rate the extent to which they experienced negative affect, positive affect, and somatic arousal, across the last week on a 5-point Likert scale (Casillas and Clark, 2020). Emotion regulation strategy usage will be assessed using the 22-item Extended Emotion Regulation Questionnaire (E-ERQ) which measures respondents’ tendency towards cognitive reappraisal, expressive suppression, distraction, selective attention, and situation selection, on a 7-point Likert scale (Guassi Moreira et al., 2024). Trait strategy usage scores will be computed by separately averaging items for each of the five strategies.

##### Physical health

3.2.1.3

Health-related quality of life will be assessed using the RAND 36-item Short Form Health Survey Instrument (SF-36), which measures domains of physical function, role disability due to physical and emotional problems, bodily pain, general health perceptions, vitality, social function, and general mental health (α > .75) (Jenkinson et al., 1994; McHorney et al., 1993; Brazier et al., 1992). To assess diet, we will use Vioscreen, a gold-standard, web-based, image-assisted, Food Frequency Questionnaire (Kristal et al., 2014), which compiles 90 days of dietary data, including what a participant has ate and drank over this time period. Dietary outputs include a personal health and nutrition summary, personal health and nutrition report, a health eating index food feedback report, top foods report, and a dietary inflammatory index report and relevant data will be used as covariates in analyses involving the microbiome data. At the in-person session, we will also collect data on participant height, weight, and BMI. Prior to the in-person session, we will obtain information on medication use, antibiotic use, supplements, alcohol use and smoking history. These variables will likely be used as covariates in analyses examining the microbiome and inflammation data.

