
### Sex interactions with health risk factors linked to AD

1.4

Obesity is one of the top modifiable risk factors for AD in the United States (Nianogo et al., 2022b) and more prevalent among women than men (Koceva et al., 2024), making it especially important to consider in terms of sex-related risk. Importantly, obesity significantly increases the risk of AD as much as 6-fold additive risk in predictive models (Kivipelto et al., 2005). However, the greater risk for AD linked to obesity is especially heightened in women – e.g., in older women, every unit increase in body mass index (BMI) is associated with a 36% increase in AD risk (Gustafson et al., 2003). Obesity not only interacts with sex, but also other risk and resilience factors for AD including education and upwards mobility. Specifically, in a prior randomized education intervention study in majority low-SES youth (Wong et al., 2014, 2022), it was shown that females randomized to attend a high-performing public charter high school had higher rates of overweight and obesity than females randomized to attend the lower-performing school (19.3% difference in rates between groups), as well as worse self-reported physical health (Wong et al., 2022; Dudovitz et al., 2018). The opposite trends were reported in males – randomization to the higher-performing schools were associated with lower rates of overweight and obesity (−14.28% difference in rates) and better self-reported physical health (9.67% difference), relative to males randomized into the lower performing schools (Wong et al., 2022; Dudovitz et al., 2018). The randomized nature of this study allows us to conclude that high quality education, previously considered a universal protective factor against AD, may in fact increase the incidence of the top modifiable risk factor for AD – obesity – in low SES females. This unintuitive and alarming finding further highlights the essential need to study how sex interacts with other important risk and protective factors for AD across the lifespan.

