The RISE-Up EA+ study leverages a natural quasi-experimental cohort that began in 2013 (RISE-Up) to understand the impact of educational experience on youth health outcomes and substance use (R01DA033362). The random admissions lottery of five high-performing charter schools in Los Angeles was initially used to find two comparable groups of adolescents that were exposed to high-and lower-performing public high schools. These groups had similar baseline demographics, prior academic performance, family characteristics, and neighborhood exposures, and have been followed longitudinally during adolescence from ages 13 through 18 (phase 1: RISE-Up-HS; R01DA033362), during their transition to emerging adulthood from ages 18 through 24 (phase 2: RISE-Up-T2A; R01DA033362), and into early adulthood from ages 24 through 28 (RISE-Up EA; R01A082868) while collecting various self-reported health metrics to understand the impact of education on health outcomes (see Fig. 1 for a timeline of study phases). (Wong et al., 2014, 2022) To assess cognitive ability and brain health, as well as associated inflammatory and microbiome-related biology, we will conduct an add on to the RISE-Up EA study (called RISE-Up EA+) to collect additional cognitive and neurobiological measures after participants began enrollment in RISE-Up EA when the cohort is aged between 24 and 26 years. Findings from earlier timepoints in the RISE-Up study position it to address the unique question of how sex-related AD risk may manifest across the lifespan. Specifically, earlier waves from grade 9 through grade 11 (RISE-Up-HS) identified that adolescents attending high-performing schools were less likely than those in lower-performing schools to engage in risky substance use and have substance using peers in their social network (Dudovitz et al., 2018). Recent results also show that young adults aged 20 and 21 (RISE-Up-T2A) that attended high-performing schools had lower rates of hazardous or dependent alcohol use, had lower cannabis misuse scores, less delinquent behaviors, and higher rates of fair/poor mental health scores (Wong et al., 2022). Differences in physical health outcomes were found between males and females, where rates of fair/poor physical health and overweight/obesity were lower for young adult males that attended high-performing schools but higher rates were found for young adult females (Wong et al., 2022). Controlling for academic outcomes (e.g., high school graduation and grade point average, standardized test scores and college matriculation) had no impact. This may indicate that the developmental pathways for later AD risk may already be in motion for females with greater mobility opportunity in the RISE-Up study (Wong et al., 2022). However, the precise biological mechanisms informing this risk are still unclear. In this paper, we will summarize the study aims, hypotheses, and protocol for the RISE-Up EA+ Study that aims to understand how factors contributing to health after mobility opportunity impact sex-related risk for developing AD later in life.

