##### Supplemental health measure: oral microbiome

3.2.5.4

While not part of the initial study design, we will collect an oral microbiome sample as a supplemental health measure to assess an additional pathway where educational experiences might modify health outcomes given preliminary evidence showing that communities of oral microbes and bacteria (Liu et al., 2023; Guo et al., 2023) as well as periodontal inflammatory metrics (Melo et al., 2025) have been altered in AD. OMNIgene OM-501 samples (DNAGenotek) will be administered during the in person visit after the scan ensuring the participants have not ingested food or water for at least 30 minutes prior to the sample. Samples will be incubated at 50 °C for 2h, vortexed, aliquoted into cryogenic tubes and then frozen at −80 °C after these preprocessing steps in lab to prepare them for shipment to the sequencing site. In addition, we will administer an adapted version of the Oral Health Questionnaire (Simpson et al., 2020) to participants to assess overall oral health, including oral hygiene behaviors and symptoms, in order to compute a total oral hygiene score (Buunk-Werkhoven et al., 2011) to be included as a covariate in analyses.

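### Aim 2 adjusts microbiome and inflammation outcomes for behaviours recorded 10 to 12 years after the lottery, so it would not estimate the total sex-specific effect of mobility opportunity; BMI's role is unclear

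*Protocol article*

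**What the plan says.** Section 3.2.1.3 (Physical health) makes two covariate statements of different strength.

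- **Diet, firm, microbiome only.** Of the food-frequency outputs it says "relevant data will be used as covariates in analyses involving the microbiome data".
- **Other variables, tentative, microbiome and inflammation.** It says "Prior to the in-person session, we will obtain information on medication use, antibiotic use, supplements, alcohol use and smoking history", and continues "These variables will likely be used as covariates in analyses examining the microbiome and inflammation data".

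Between the two stands a sentence on body size: "At the in-person session, we will also collect data on participant height, weight, and BMI". It gives BMI no analysis role, and the text does not settle whether BMI is among the variables meant.

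Neither statement is labelled as a sensitivity, direct-effect or mediation analysis.

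The target is set in Section 2. H2 compares mobility with static opportunity and expects more inflammatory blood and stool profiles in females but not in males. Section 5 (Discussion) says that the lottery design permits causal conclusions about exposure to high-performing schools.

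**The concern.** The exposure is a lottery at entry to 9th grade. The covariates are recorded when participants are 24 to 26, so the exposure may have changed them. The article supplies reasons to think that it did:

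- Section 1.1 names health behaviours as one way in which education may lower AD risk.
- Section 1.7 reports that "young adults aged 20 and 21 (RISE-Up-T2A) that attended high-performing schools had lower rates of hazardous or dependent alcohol use".
- Section 1.4 reports: "females randomized to attend a high-performing public charter high school had higher rates of overweight and obesity than females randomized to attend the lower-performing school", with the opposite pattern in males.

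Two things are at stake. First, holding a consequence of the lottery constant removes whatever part of the lottery's effect runs through it. What remains is at best a direct effect, whereas H2 is worded as the overall difference between the groups. Second, the lottery balances the groups on pre-lottery causes only. Within levels of a post-lottery behaviour that balance is lost, because unmeasured causes shared by the behaviour and the outcome become associated with lottery group. A null Aim 2 result could then reflect over-adjustment, and a positive one would not be the total causal effect that the Discussion describes.

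**Working it through.** **1. Timing.** Median age at baseline was 14.2 (Section 3.1) and extension participants are 24 to 26. 24 - 14.2 = 9.8 and 26 - 14.2 = 11.8, so the gap is about 10 to 12 years.

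**2. The plan's own figure.** Section 4 gives 80% power for d = 0.36 with 150 per group at alpha 0.025. The noncentrality is 0.36 x sqrt(150 x 150 / 300) = 3.118, the critical t on 298 df is 2.253, and power is 80.6%. The figure reproduces and is not in dispute. It concerns brain health; no power figure is stated for Aim 2.

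**3. What adjustment removes.** Let a_F and a_M be the lottery's effect on a covariate in females and males, and b the covariate's effect on the outcome in SD, taken as equal in the sexes. In each sex:

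total effect = direct effect + a x b

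Adjustment leaves the direct effect, if there are no unmeasured common causes. It removes a_F x b in females, a_M x b in males, and (a_F - a_M) x b from the mobility-by-sex contrast.

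**4. Named covariates.**

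| Covariate | Lottery effect reported in the article | What follows |
|---|---|---|
| Alcohol | Hazardous use lower in those who attended high-performing schools; no sex split | Effect within each sex shifts by a x b; interaction unchanged if a_F = a_M, otherwise unknown |
| Smoking | Only through lower risky substance use in general | Not computable |
| Diet | None reported | Not computable |
| Medication, antibiotics, supplements | None reported | Not computable |

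The sign for alcohol need not favour the null. If a is negative and b is positive (assumption), a x b is negative. The adjusted mobility effect is then more pro-inflammatory than the total effect, which in females is the direction that H2 expects.

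**5. BMI, if it is a covariate.** Inputs from Section 1.4, read as percentage points: a_F = +0.193 and a_M = -0.1428 for overweight or obesity. Then a_F - a_M = 0.193 + 0.1428 = 0.3358. Section 1.5 links obesity to inflammation and to the microbiome but gives no standardised size, so b is assumed.

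| Assumed b (SD) | Removed in females | Removed in males | Removed from the contrast |
|---|---|---|---|
| 0.2 | 0.039 | -0.029 | 0.067 |
| 0.5 | 0.097 | -0.071 | 0.168 |
| 0.8 | 0.154 | -0.114 | 0.269 |

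**6. Check by simulation.** A linear model with mobility, sex and their interaction was fitted with and without overweight status. Settings: 75 per cell, mean overweight rate 45% (assumed), outcome SD 1, true contrast 0.715 SD, 4,000 runs per scenario. The mean estimated contrast moved from 0.718 to 0.649 at b = 0.2, from 0.713 to 0.547 at b = 0.5, and from 0.712 to 0.445 at b = 0.8. The drops of 0.069, 0.166 and 0.266 agree with the formula. At b = 0 nothing was lost (0.720 and 0.721).

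**The case against.** The strongest reply is that little is fixed. Apart from diet, the wording is tentative, the article has no detailed analysis section, and covariate sets are commonly left to a statistical analysis plan that is not shown. The lack of a named unadjusted model is indeed no fault of the article. But the point rests on covariates that the article does name, with diet stated firmly, so that reply does not dispose of it.

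A second reply has force. The study wants stable, trait-like immune profiles rather than acute responses (Section 3.2.5.1). Recent antibiotics, medication and supplements can then be treated as measurement nuisance, and adjusting for them is defensible.

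Several stronger readings are tempting and lack support:

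- **That the plan biases Aim 2 towards no moderation by sex.** The article gives opposite effects by sex only for overweight, and BMI is not clearly a covariate. For alcohol, diet and smoking no sex-specific lottery effect is reported.
- **That diet and alcohol would remove still more.** Nothing in the article shows this, and the alcohol adjustment could act the other way.
- **That inflammation outcomes are adjusted for diet, or that the dietary inflammatory index is a fixed covariate.** Diet is tied to microbiome analyses, and only to whatever dietary data are judged relevant.
- **That the loss is a stated share of the detectable effect.** That would borrow the brain-health calculation for Aim 2.
- **That the oral-hygiene score, which is "to be included as a covariate in analyses", belongs to this problem.** It concerns a supplemental oral sample (Section 3.2.5.4), whereas Aim 2 concerns blood and stool.

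**Conclusion.** The concern holds in a limited form. If the covariate statements are followed for the main Aim 2 models, those models do not estimate the total effect of mobility opportunity within each sex, and they give up part of the protection that the lottery provides. This rests on the timing and on the article's own account of health behaviours, and needs no assumed figure.

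No size can be given for the covariates actually named, and the direction of any change in the interaction is undetermined. The only size available is conditional on BMI being adjusted for: about 0.07 to 0.27 SD off the mobility-by-sex contrast. It assumes an overweight effect of 0.2 to 0.8 SD, equal in the sexes. It also assumes that the earlier-phase overweight difference persists to ages 24-26; Section 1.7 places this pattern at ages 20 and 21, and Section 5 notes that the cohort's earlier health data are self-reported.

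**What to change.** State the primary Aim 2 model as lottery group, sex, their interaction, pre-lottery covariates, and technical sample factors such as assay batch, collection device and collection occasion. Move diet, alcohol, smoking and BMI to an analysis labelled as sensitivity, direct-effect or mediation, and say explicitly whether BMI is a covariate anywhere. Recent antibiotic and medication use may stay as measurement-nuisance factors, with that reason given, or be handled in a sensitivity analysis.

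The change is one of wording and needs no new data. Its price is somewhat more residual variance in the primary microbiome model, since diet would no longer absorb any of it.
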